## 5. Conclusions

Due to a great number of patients suffering from severe AS with concomitant coronary artery disease, proper diagnostic steps in the assessment of coronary artery stenosis severity still need to be established. Therefore, we aim to perform a first proof-of-concept study in which intracoronary indices will be measured before and after TAVI, and compared to quantitative myocardial perfusion CZT-SPECT. As a next step, we will define cut-off values of FFR, CFR, and IMR reflecting the decreased coronary blood flow and significant stenosis.

## Figures and Tables

**Figure 1 biomimetics-07-00230-f001:**
[figure not shown]
Study design and first endpoint.

**Figure 2 biomimetics-07-00230-f002:**
[figure not shown]
Summary of a second endpoint.

**Table 1 biomimetics-07-00230-t001:** The summary of inclusion and exclusion criteria.

Inclusion criteria
Severe aortic valve stenosis qualification for TAVI by the heart team
Presence of an intermediate (30%–70%) coronary lesion in LAD
**Exclusion criteria**
Patients who are hemodynamically unstable
LVEF < 50%
Pregnancy or lactation
Contraindications to adenosine
Chronic kidney disease (eGFR < 30 mL/min/1.73 m^2^)
Coronary artery disease which requires revascularisation
CABG in the past

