### 2.4. Sample Size

Our target sample size is set at 40 patients for a proof-of-concept study. No power calculations were performed since this is currently a pilot study and relevant data on our research objectives regarding the comparison between patients suffering from AS with CFR and IMR assessment are lacking. The results of this study will be used to design a larger study in the near future. Since the total number of patients for AS diagnosis in the Division of Cardiology and Structural Heart Diseases is estimated at 100 a year, we expect that our target number of patients can be included within one year.

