### 2.6. SPECT Protocol

We plan to perform a 1-day protocol. Patients will be instructed not to consume chocolate and caffeine products 24 h before the test. Dynamic MPI-SPECT will be performed on a dedicated CZT-SPECT camera (D-SPECT Cardio, Spectrum Dynamics Medical). After the patient’s heart positioning within the field of view with the use of intravenous administration of an initial dose of approx. 37 MBq of ^99m^Tc-MIBI, an intravenous bolus infusion of 3.5 MBq/kg of ^99m^Tc-MIBI at a rate of 1–2 cm^3^/s using an automatic syringe pump will start for the resting dynamic scan. After a 25 min delay, an 8 min resting static perfusion scan will be performed.

In the next stage, we will inject 0.4 mg of regadenoson for the stress phase. Regadenoson bolus will be flashed with 5 mL 0.9% NaCl and 1 min after the injection, a stress phase list-mode acquisition will start with the administration of a second bolus of ^99m^Tc-MIBI (10 MBq/kg or 3× resting dose) at peak hyperaemia. Then after a 25 min delay a stress static perfusion scan will be conducted. Rest-stress dynamic acquisitions will be completed in about 75 min. List-mode data will be rebinned into 32 frames consisting of 21 × 3 s, 1 × 9 s, 1 × 15 s, 1 × 21 s, 1 × 27 s, and 7 × 30 s frames. During the rest and stress phase, monitoring of heart rate and rhythm, blood pressure, pulse oximetry, and electrocardiography (ECG) will be performed. Myocardial perfusion will be reported based on a 17-segment model of the heart [13]. For each segment, a coronary flow reserve (CFR) will be calculated with dedicated software (Corridor 4DM, INVIA, USA).

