#### 2.8.4. Calculation of Myocardial Blood Flow by SPECT

The time-activity curves (TAC) for the input function will be derived automatically after correction for motion artefacts. As a first step, to calculate myocardial retention rate a previously described model will be used [19]. As a second step, to convert the retention rate to myocardial blood flow values, the Renkin–Crone flow model will be used [19]. In the end, CFR will be calculated by dividing MBF in stress by MBF in rest. As a next step, the CFR measured by CZT-SPECT will be matched with FFR, CFR, and IMR calculated in LAD.

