### 2.9. Statistical Analysis

Normally distributed quantitative variables will be presented with mean, standard deviation, and 95% confidence interval. Non-normally distributed data will be presented with median and interquartile ranges. The difference between intracoronary indices values before and after TAVI will be assessed with Student *t* or Mann–Whitney *U* tests as appropriate. Sensitivity, specificity, positive predictive value (PPV), and negative predictive value (NPV) of intracoronary indices measured in LAD will be calculated on a per-patient basis. Receiver operator characteristic (ROC) curves will be constructed for FFR, CFR, and IMR to determine diagnostic cut-off values. Correlations between intracoronary indices and MBF measured by CZT-SPECT will be assessed using Pearson’s correlations. A statistically significant difference will be defined as a two-sided *P* value less than 0.05. The missing data will be labelled.

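### As published, the entry criteria admit limited LAD-territory infarct scar, which can turn the SPECT reference positive without a flow-limiting stenosis and lower the reported accuracy of FFR

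*Protocol article*

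**What the plan says.** **Entry.** The coronary inclusion criterion in Table 1 is "Presence of an intermediate (30%–70%) coronary lesion in LAD". There are seven exclusions: haemodynamic instability, LVEF below 50%, pregnancy or lactation, contraindications to adenosine, eGFR below 30, "Coronary artery disease which requires revascularisation" and "CABG in the past". Section 2.3 refers to Table 1 for the criteria and adds no further exclusion. Previous myocardial infarction is mentioned nowhere in the article.

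**Reference.** Section 2.8.4 defines the SPECT flow reserve as stress flow divided by rest flow and says that "the CFR measured by CZT-SPECT will be matched with FFR, CFR, and IMR calculated in LAD". Section 2.2 makes cut-offs for significant stenosis the secondary objective. Section 2.9 derives them from ROC curves and adds per-patient sensitivity, specificity, PPV and NPV. In section 5, reduced flow and significant stenosis are treated as one target.

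**Scan at hand.** Under section 2.6, "an 8 min resting static perfusion scan will be performed" in every patient.

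**Size.** Section 2.4: "Our target sample size is set at 40 patients for a proof-of-concept study", and "No power calculations were performed since this is currently a pilot study".

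**The concern.** The cut-off analysis needs a low LAD-territory flow reserve to mean that the LAD lesion limits flow. A healed infarct in the same territory can break that link, because scarred segments may show low flow reserve whatever the stenosis.

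None of the listed exclusions closes this gap. LVEF below 50% removes many large anterior infarcts but not small or non-transmural ones. A healed infarct need not require revascularisation. The CABG criterion concerns grafts.

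A scar patient who is reference-positive without a flow-limiting stenosis will tend to have an FFR like that of the negatives, and so counts as a false negative for FFR. With 40 patients, a handful of such cases is a visible share of the positives. Sensitivity is a planned output, and section 2.4 says the results will be used to design a larger study.

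**Working it through.** The plan states no figure that can be reproduced here: the 40 has no power calculation behind it, and there is no infarct rate. Everything below except N = 40 is an assumption.

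**1. How many patients could be affected?** With p the share with LAD-territory infarction, the expected number is 40p and the chance of at least one is 1 − (1 − p)^40.

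| p | Expected of 40 | P(at least one) |
|---|---|---|
| 2% | 0.8 | 55% |
| 5% | 2 | 87% |
| 10% | 4 | 98.5% |
| 15% | 6 | 99.8% |

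**2. Largest possible share of the positives.** If 35% are reference-positive, that is 0.35 × 40 = 14. Two to six scar patients (5–15%) would be 2/14 = 14% to 6/14 = 43% of them. This assumes that every scar patient is reference-positive because of scar, so for these inputs it is an upper bound.

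**3. Sensitivity at a fixed cut-off.** Assume 12 patients positive through stenosis, sensitivity 0.85 and specificity 0.80 for stenosis-caused low flow, and k further patients positive through scar only. Apparent sensitivity = (12 × 0.85 + k × 0.20) / (12 + k).

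- k = 0: 10.2/12 = 0.85
- k = 2: 10.6/14 = 0.76
- k = 4: 11.0/16 = 0.69
- k = 6: 11.4/18 = 0.63

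**4. ROC simulation, every scar patient reference-positive.** 4,000 runs; FFR ~ N(0.76, 0.06) in 12 true positives and N(0.86, 0.06) in the other 28, of whom k are labelled positive because of scar; cut-off by the Youden index.

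| k | Mean AUC | Mean FFR cut-off | SD of cut-off |
|---|---|---|---|
| 0 | 0.88 | 0.804 | 0.024 |
| 2 | 0.83 | 0.804 | 0.026 |
| 4 | 0.79 | 0.806 | 0.028 |
| 6 | 0.76 | 0.811 | 0.029 |

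**5. Partial conversion.** The same model was rerun with 30% to 100% of scar patients turning the reference positive, and with their mean FFR either equal to that of the other negatives or 0.02 higher. AUC is about 0.81–0.86 with two scar patients and 0.76–0.85 with four. The low end needs full conversion and the higher FFR; the high end is 30% conversion. With two or four scar patients the mean cut-off stays within 0.804–0.807.

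**Reading.** The loss is in AUC and sensitivity. Even six fully converted cases move the mean cut-off by only 0.811 − 0.804 = 0.007, about a quarter of its own sampling SD.

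**The case against.** **This is an omission from a condensed article.** Table 1 is captioned as a summary, and a full protocol could hold another criterion or a rule for fixed defects. That lowers confidence. But eligibility is what this article does set out, and the list as published admits these patients.

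**Scar partly cancels.** The reference is a stress/rest ratio, so scar that lowers both flows may leave it nearly unchanged, and small scar with preserved LVEF is the subset least likely to drive a territory-level value. This stands. How often scar alone makes the reference positive cannot be computed from the article, which is why a range from 30% to 100% is shown.

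**The cut-off is the deliverable, and it barely moves.** This also stands. A reader might infer that a few infarct patients would push the FFR cut-off materially upward; the simulation does not support that. A reader might also infer that scar would create a false association of IMR with significant stenosis. The article contains nothing on IMR in infarcted myocardium, so that claim is not made here. Nor does the article say why CABG is excluded, so it cannot be said that the sponsor applied a principle inconsistently.

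**The reference already has non-stenotic contributions.** Section 3 notes that aortic stenosis itself raises resting flow and lowers hyperaemic flow. But every enrolled patient has severe aortic stenosis, whereas scar affects only some and can be identified from a scan already planned.

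**It is a pilot.** True, and this keeps the point moderate. Its accuracy estimates are nonetheless meant to inform the next study.

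**Conclusion.** The point holds in a limited form. As published, the criteria admit patients with limited LAD-territory infarction and LVEF of 50% or more, and in some of them scar rather than the LAD lesion can make the reference positive.

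At an assumed 5–10% (2–4 of 40), the AUC of FFR falls from about 0.88 to 0.76–0.86 and sensitivity falls as well. The spread of the cut-off widens slightly and its mean stays almost where it was. These sizes rest on an infarct rate, a conversion rate and FFR distributions that the article does not give. The share of 14–43% of positives due to scar is a ceiling, not an estimate. The point merits a change because the remedy is cheap; it does not invalidate the design.

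**What to change.** Preferred, with entry unchanged: use the resting static CZT-SPECT that section 2.6 already schedules.

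1. Identify LAD segments with a fixed resting defect and leave them out of the LAD-territory flow reserve.
2. Run the ROC, sensitivity, specificity, PPV and NPV analyses without patients whose LAD territory is mostly fixed defect. At minimum, prespecify this as a sensitivity analysis.
3. Keep these patients in the before/after analysis, where each is compared with their own baseline.

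Alternative: add previous myocardial infarction in the LAD territory to the exclusions in Table 1. If the full protocol already has such a criterion, state it in the table.

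Cost: one analysis rule or one line in Table 1, with no extra scan or procedure. The cut-off analysis loses a few patients, and the cut-offs apply to a slightly narrower TAVI population.

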## Data Availability

Not applicable.
